### Participants

All participants will be attending either the Sydney or Brisbane Recovery Service Centres. For the purpose of the current study, only people diagnosed with an alcohol or substance abuse problem will enter the study. It is expected that over the course of the study approximately 200 people will be recruited to participate. Previous surveys of people attending Australian Recovery Service Centres indicate that on average participants are 37 years of age (SD = 9.90) and have had long-term substance abuse problems (M = 19 years; SD = 23.10). On average, alcohol is the most commonly reported primary substance of abuse (55.6%), followed by amphetamines (20.8%), cannabis (9.7%), heroin (6.2%) and others [7.7%; [27]]. All participants will complete informed written consent prior to commencing the study, and all participants will be over the age of 18.

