#### Outcome measures

Baseline assessments will be conducted prior to notification of randomization status. This will include administering the Structured Clinical Interview of the DSM IV [SCID; [32]] to identify 12-month and lifetime history of alcohol or other substance abuse and dependence disorders. Additionally, 12-month and lifetime history of depressive disorders will also be assessed using the SCID. Outcome measures will be collected at baseline, weekly during the 5 weeks of the treatment program and then at 3-, 6-, 9-, and 12-month follow-up (see Table 1 for schedule). Independent assessors, who will remain blind to intervention allocation, will conduct follow-up telephone assessments to collect this data. Each participant will be offered $20 AUD for completion of the baseline assessment and each subsequent follow-up assessment, as reimbursement for the time associated with completing the measures. Participants will receive $10 AUD for each assessment completed during the treatment program. For assessments completed while a participant is a resident at the Recovery Service Centre, he or she will be remunerated in cash. For telephone assessments completed once the participant leaves the program, gift certificates will be mailed out.

**Table 1 T1:** Assessment instruments proposed for the current study

Domain assessment and instrument used	Baseline	Weeks	Week	Months
		
		1 to 4	5	3, 6, 9,12

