#### Primary outcome measures

The two primary outcome variables will be: a) level of substance use; and b) level of depression. The level of substance use will be measured using the composite scores for alcohol use and drug use from the Addiction Severity Index - 5^th ^Edition [ASI; [33]]. The ASI is a semi-structured clinical interview that has been used widely in addiction research [34]. The Opiate Treatment Index [OTI; [35]] will be used as an alternate measure of alcohol and substance use in the last month. The OTI yields a score reflecting the mean number of substance use occasions per day for each drug class assessed for the month prior to assessment. The Timeline Follow-Back Method [TLFB; [36]] will be used to improve participants' recall of their alcohol and substance use on the ASI and OTI. The TLFB method yields high test-retest reliability and has been used successfully in both face-to-face and telephone delivered assessment procedures [37,38]. The Beck Depression Fast Screen [BDFS; [39]] and the depression subscale of the Depression, Anxiety and Stress Scale [DASS-21; [40]] will be used to examine changes in depression levels during the course of the study.

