### Data-analysis

#### Power analysis

Data from the SHADE study [25] indicate that the computerized intervention is associated with a 1.53 effect size change for depression and 0.86 for alcohol between baseline and 12-month follow-up assessments. These effects sizes were entered into G-Power 3.1 [49] in order to estimate the sample sizes required to detect similar differences between the treatment and active control conditions in the current study. Power was set at 80% and conservative 2-tailed tests were assumed even though a directional hypothesis is proposed. The sample size needed to detect a similar effect size between groups on depression is 8 per group for depression (total N = 16) and 23 per group for alcohol (total N = 46). Given the SHADE studies compared the computerized intervention to a control condition consisting of only received a brief intervention and the proposed study is comparing SHADE + TAU to an active control condition + TAU, we anticipate smaller effect sizes. When a more conservative medium effect size of .50 is used, power is set to 80% and a 2-tailed test is used, a sample size of 64 per group is needed (total N = 128). A conservative drop out rate is 35% of participants at follow-up. As such, we will recruit a minimum of 200 participants to the study. This will ensure that we will have sufficient power to conduct the analysis.

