#### Analysis plan

Data coding and analysis will be carried out by the authors using available software packages. Variables hypothesised to change over time according to treatment allocation will be examined predominantly using generalized linear mixed models. These techniques facilitate management of missing data without imputing values or excluding participants. Primary outcome measures will typically be analysed in two ways: a) intention to treat; and b) analyses performed within the sub-sample of participants who completed the majority of treatment sessions. In addition, comparisons on selected demographic and clinical characteristics will be made between this sub-sample and those who dropped out of treatment, to help detect any biases in outcome measures. Other potential confounders will also be examined (e.g. involvement in additional mental health treatments) and their potential effects will be modelled in the major analyses (e.g., controlling and not controlling for these variables). As a partial control for the number of statistical tests to be conducted, the threshold for significance will be set at p < 0.01.

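### No primary contrast is named among at least five primary measures, and the p < 0.01 threshold conflicts with a sample size that was calculated at 0.05

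*Protocol article*

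**What the plan says.** All references are to the Protocol article.

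- **Primary outcome measures:** "The two primary outcome variables will be: a) level of substance use; and b) level of depression". Substance use is scored by the Addiction Severity Index (ASI) alcohol composite and the ASI drug composite. The Opiate Treatment Index (OTI), which gives one score per drug class, "will be used as an alternate measure of alcohol and substance use in the last month". Depression is measured by the Beck Depression Fast Screen (BDFS) and the depression subscale of the DASS-21, with neither put ahead of the other.
- **Outcome measures:** data are collected at baseline, weekly during treatment, "then at 3-, 6-, 9-, and 12-month follow-up". No time point is named as primary.
- **Analysis plan:** the approach is predominantly generalized linear mixed models. Primary outcomes are analysed by intention to treat and again in those who completed most sessions. Confounders are both controlled for and not controlled for. The threshold is stated as "As a partial control for the number of statistical tests to be conducted, the threshold for significance will be set at p < 0.01".
- **Power analysis:** "Power was set at 80% and conservative 2-tailed tests were assumed even though a directional hypothesis is proposed". For an effect of 0.50, "power is set to 80% and a 2-tailed test is used, a sample size of 64 per group is needed (total N = 128" is the stated result. With 35% dropout, the target is at least 200. The significance level used is not stated.

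**The concern.** There are two linked problems.

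**No primary contrast.** A construct is not a test. With two depression scales of equal rank, several substance-use scores and four follow-ups, a favourable result on any one of them could be reported as success on a primary outcome. The 0.01 threshold is meant to offset this, but the family of tests it covers is not defined, so nobody can say what overall error rate it gives.

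**Threshold and sample size disagree.** If the sample size was calculated at 0.05 and the analysis is judged at 0.01, the stated 80% power does not apply to the analysis planned. A real effect of the size the trial was designed to find would be missed more often than the article says.

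**Working it through.** **Step 1. Reproduce the plan's sample sizes.** Inputs from Power analysis: effects 1.53 (depression), 0.86 (alcohol) and 0.50; 80% power; two-tailed; equal groups. Method: two-sample t-test using the noncentral t distribution. Participants needed per group:

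| Effect | Stated | Two-sided 0.05 | One-sided 0.05 | Two-sided 0.01 |
|---|---|---|---|---|
| 1.53 | 8 | 8 | 7 | 12 |
| 0.86 | 23 | 23 | 18 | 34 |
| 0.50 | 64 | 64 | 51 | 96 |

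All three stated figures match two-sided 0.05 exactly and none matches 0.01. For dropout, 128 / (1 − 0.35) = 197, which is consistent with the target of 200.

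**Step 2. Power at the planned threshold.** Evaluable sample: 200 × 0.65 = 130, or 65 per group. Noncentrality = 0.50 × √(65/2) = 2.85, with 128 degrees of freedom.

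| Two-sided level | Critical t | Power at d = 0.50 | Detectable d at 80% power |
|---|---|---|---|
| 0.05 | 1.98 | 80.8% | 0.50 |
| 0.025 | 2.27 | 71.9% | 0.55 |
| 0.01 | 2.61 | 59.4% | 0.61 |

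Moving from 0.05 to 0.01 costs 80.8 − 59.4 = 21.4 percentage points. Restoring 80% power at 0.01 would need 2 × 96 = 192 evaluable, or 192 / 0.65 = 296 recruited.

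**Step 3. Count the primary variables.** ASI alcohol, ASI drug, OTI, BDFS and DASS-21 depression make five if the OTI counts once, and more if each drug class counts.

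**Step 4. What 0.01 controls.** For k independent tests, family-wise error is 1 − 0.99^k.

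- k = 5: 4.9%
- k = 6: 5.9%
- k = 20 (five measures × four follow-ups, intention to treat only): 18.2%

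Positive correlation lowers these figures. A multivariate normal simulation assumed correlations of 0.3-0.7 between measures and 0.5-0.7 between times. It gave 3.5-4.7% for five tests and 9.7-15.5% for 20. The correlations are assumptions; the article gives none.

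**The case against.** **The count of 20 is not in the article.** Mixed models for variables expected to change over time by allocation can naturally be read as one group-by-time test per measure. Five such tests give 4.9%, and four (with the OTI set aside as the alternate) give 3.9%, so 0.01 would then suffice. This stands as a possible reading. But the article does not commit to it, and scoring the OTI by drug class takes the count past five.

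**Only partial control is claimed.** This is correct. A reader might infer that the plan breaks a promise to control false positives, or that 0.01 fails outright. Neither is supported: the fault is an undefined family and an unnamed primary contrast.

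**Some ordering is implied.** The OTI is called an alternate measure, and the prior-trial effects cited ("the computerized intervention is associated with a 1.53 effect size change for depression and 0.86 for alcohol between baseline and 12-month follow-up assessments") point to 12 months. That is fair, but it does not choose between the depression scales or name 12 months as the primary time point.

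**A fuller document may settle the contrast.** It may, and a missing contrast alone would be weak grounds. But the article itself sets the primary outcomes and the threshold, and the conflict between 0.01 and the sample size lies wholly within it.

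**Mixed models keep participants with partial data.** True, so 59% is an approximate figure on the plan's own t-test basis. With no dropout at all (100 per group), power at 0.01 would be 82%.

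Two stronger readings should be set aside:

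- Multiplying by two populations and two adjustment versions gives 80 tests and 55% if independent. Those analyses largely repeat the same comparisons and may be meant as supportive. Under further assumed correlations (0.85 between populations, 0.95 between adjustments) the simulated figure is 18-29%.
- The survey figure of 55.6% with alcohol as primary substance might suggest that the alcohol effect is diluted to 0.556 × 0.50 = 0.28. That requires no alcohol benefit at all in the other 44.4%, which the article does not support. The composites are scheduled for everyone, and the survey describes earlier residents.

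**Conclusion.** The point holds in two parts.

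First, the article leaves the primary contrast open across at least five variables and four follow-ups, and its flat threshold limits overall error to 5% only if there are at most five tests. Testing five measures at each follow-up would give 18% if independent, or about 10-16% under the assumed correlations. These figures depend on that way of testing, which the article neither states nor rules out.

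Second, and independent of any test count, the threshold and the sample size are inconsistent. The stated numbers imply two-sided 0.05. At 0.01, power for an effect of 0.50 with 65 per group is about 59% rather than 80%, on a t-test basis with 35% dropout and allowing for some recovery through mixed models. The statement that 200 participants give sufficient power is therefore not supported at the threshold the analysis will use.

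**What to change.** Before unblinding, amend the plan to:

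1. Name one depression scale and one substance-use measure that applies to all participants, derived from data already scheduled. The Timeline Follow-Back is described only as a recall aid, so an outcome built on it would have to be defined explicitly.
2. Give each one mixed-model contrast, in the intention-to-treat set, at one time point. Twelve months matches the effect sizes cited in Power analysis; another choice can be defended if it is fixed in advance.
3. Test the two with Holm at overall two-sided 0.05, in place of the flat 0.01.
4. Label the other scales, OTI drug classes and time points as secondary, and the completer and confounder-adjusted analyses as secondary or sensitivity.
5. Restate power at the threshold used. With 65 per group, that is about 72% for an effect of 0.50 at the stricter Holm step of 0.025, or a detectable effect of about 0.55 at 80% power.

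The change needs an amendment and revised wording but no new assessments; recruitment was still under way when the article was written. The trial gives up claiming success on an alternate scale or time point. It also has to state a lower power figure than the 80% now given, although 72% is better than the 59% the present threshold provides.

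### The sample size of 64 per group implies a two-sided alpha of 0.05, but significance is set at p < 0.01; by the protocol's own method the power for d = 0.50 is then about 59%, not 80%

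*Protocol article*

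**What the plan says.** Under Power analysis, the protocol article first enters effect sizes of 1.53 (depression) and 0.86 (alcohol) from the earlier SHADE study and obtains 8 and 23 per group. It fixes the power at 80% and notes that "conservative 2-tailed tests were assumed even though a directional hypothesis is proposed". It then expects smaller effects, because both arms receive usual treatment and the comparator is active. So it repeats the calculation for a standardised effect of 0.50, with power and sidedness unchanged, and finds that "a sample size of 64 per group is needed (total N = 128". With an allowance of 35% for dropout it sets a minimum of 200 recruits and concludes: "This will ensure that we will have sufficient power to conduct the analysis". No alpha is given anywhere in that section.

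The next section, Analysis plan, describes the mixed models and the two analyses of the primary outcomes. Its last sentence fixes the decision rule: "the threshold for significance will be set at p < 0.01". The reason it gives is the number of tests. Nothing there limits the stricter threshold to secondary or exploratory tests.

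**The concern.** A sample size delivers its stated power only at the significance level for which it was computed. Here the level that decides the result is 0.01, while the level behind the sample size appears to be 0.05. If so, the assurance of sufficient power does not apply to the analysis described immediately after it. The stricter threshold does no harm to the type I error. What is at stake is the type II error: on the protocol's own assumptions, the chance of missing an effect of the planned size rises from about 19% to about 41%. Anyone weighing a non-significant result against the published 80% would be using the wrong figure.

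**Working it through.** **Inputs from the Power analysis section:** d = 0.50 (so SD = 1), power 80%, two-tailed test, equal groups, 35% dropout, minimum 200 recruited, and stated sizes of 8, 23 and 64 per group for d = 1.53, 0.86 and 0.50. **Input from the Analysis plan section:** threshold 0.01.

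**Method.** Two-sample t-test with the noncentral t distribution. With n per group, the noncentrality is d × √(n/2) on 2n − 2 degrees of freedom. Power is the probability that |t| exceeds the two-sided critical value.

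**Step 1: recover the alpha.** Size per group for 80% power, two-sided:

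| d | stated | alpha 0.05 | alpha 0.01 |
|---|---|---|---|
| 1.53 | 8 | 7.8, so 8 | 11.7, so 12 |
| 0.86 | 23 | 22.2, so 23 | 33.3, so 34 |
| 0.50 | 64 | 63.8, so 64 | 95.1, so 96 |

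All three stated figures match at 0.05 and none at 0.01. For d = 0.50, a one-sided test would give 51 at alpha 0.05 and 82 at alpha 0.01, so neither of these explains 64. Alpha 0.05 is an inference, but three figures agree on it.

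**Step 2: numbers analysed.** 128 / (1 − 0.35) = 196.9, so 197, which the protocol rounds up to 200. Then 200 × 0.65 = 130, or 65 per arm.

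**Step 3: power at 65 per arm, d = 0.50.** Noncentrality = 0.50 × √(65/2) = 2.85 on 128 degrees of freedom.

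- Alpha 0.05: 80.8%. The protocol's claim is reproduced.
- Alpha 0.025: 71.9%.
- Alpha 0.0125: 62.5%.
- Alpha 0.01: 59.4% (58.5% at exactly 64 per arm).

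**Step 4: what 80% power would take at 0.01.** At 65 per arm the detectable effect is d = 0.607, about 0.61. For d = 0.50, 96 per arm are needed: 192 analysed, and 192 / 0.65 = 295.4, so 296 recruited.

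**Step 5: how much a better analysis could recover.** The protocol gives no correlation, so this step rests on assumed values. Adjusting for a baseline score with correlation r to the outcome divides the residual SD by 1/√(1 − r²), so the effective effect is 0.50 / √(1 − r²). At 65 per arm and alpha 0.01:

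| assumed r | effective d | power |
|---|---|---|
| 0 | 0.500 | 59% |
| 0.3 | 0.524 | 65% |
| 0.5 | 0.577 | 75% |
| 0.57 | 0.609 | 80% |
| 0.6 | 0.625 | 83% |

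The break-even is r = √(1 − (0.50/0.607)²) = 0.57.

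**The case against.** The strongest reply is that the trial will not be analysed by an unadjusted t-test on completers. The Analysis plan section specifies mixed models that keep participants with partial data, and Table 1 schedules primary-outcome scores at baseline, week 5 and four follow-ups. A reader might therefore infer from the 59% that the trial itself has only 59% power. The document does not support that. A baseline correlation of 0.57 or more would bring power at 0.01 back to 80%, and with no loss at all (100 per arm) even the simple comparison would have 82%. This part of the reply stands. It does not rescue the power statement, because the protocol states no correlation, takes no credit for repeated measures, and itself plans for 35% loss.

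It can also be said that alpha 0.05 is never stated. That is true, and it should be called implied, but no other alpha and sidedness tried returns the stated figures.

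A third reply is that 0.01 may be meant for secondary tests only. The text does not say so; if that is the intention, it needs to be written down.

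A fourth concerns the remedy. It is tempting to apply Holm at once to the two primary outcomes and quote 72% to 81%. As the protocol stands, this does not work. The Primary outcome measures section names two constructs but measures them with at least four scores (ASI alcohol, ASI drug, the Beck fast screen and DASS-21 depression), adds the OTI as an alternative, and there are four follow-up times. Over four scores the first Holm step is 0.05 / 4 = 0.0125, where power is only 62%.

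**Conclusion.** The inconsistency is real. The sample size rests on an implied two-sided alpha of 0.05, the decision threshold is 0.01, and nothing in the protocol article reconciles them. By the protocol's own two-group method, with d = 0.50 and 65 per arm after 35% loss, power at the stated threshold is about 59%, not 80%, and the effect detectable with 80% power is d = 0.61.

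The finding is that the power statement is unsupported at the trial's own threshold. It is not that the planned mixed models have been shown to be underpowered: their power depends on correlations the protocol does not give, and under assumed baseline correlations of 0.3 to 0.6 it would run from about 65% to 83%. Nor does it imply bias, since the stricter threshold lowers the false-positive rate. A reader might go further and expect a null result to be taken as proof that SHADE adds nothing; the document says nothing of the kind.

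**What to change.** Make the power statement and the threshold agree. Either route will do.

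1. **Keep p < 0.01 throughout and restate power.** Suggested wording: *130 analysed gives about 59% power for d = 0.50 and 80% power for d = 0.61 at two-sided p < 0.01.* If credit is to be taken for baseline adjustment or repeated measures, state the assumed correlation and its source. This route needs no other change to the plan.

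2. **Give the primary outcomes their own alpha.** Before unblinding, name one measure and one time point for each of the two primary constructs. Apply a family-wise 0.05 by Holm (0.025, then 0.05) to those two tests and keep p < 0.01 for all others. Only then state per-test power for d = 0.50 at 65 per arm: 72% at 0.025 and 81% at 0.05. This loosens a threshold adopted for multiplicity while recruitment is already under way, so the change should be dated and justified.

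In both cases state the alpha in the Power analysis section. The cost is wording, a less favourable power figure and, under the second route, the choice of a single measure and time point per construct. Neither needs more participants. The 200 is a minimum, so recruiting more is not excluded; regaining 80% power for d = 0.50 at 0.01 by the same method would take about 296.

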## Discussion

The present study is examining the effectiveness of 'adding' a computer delivered co-morbidity intervention to residential alcohol and other substance abuse treatment. A large proportion of people accessing residential drug and alcohol treatment screen positive for mental illness, with depression being the most common [1]. It is expected that long-term mental health outcomes for participants who complete the SHADE program will be significantly better than for those allocated to the control condition. Additionally, as the residential treatment facility is based on a 12-step approach, rather than a CBT approach, it is expected that the CBT based SHADE intervention will also improve alcohol and substance abuse outcomes for participants relative to the control condition.

### Strengths and limitations

A significant strength of the current research is that it will be conducted as an effectiveness study. Unlike efficacy studies, where clinical trials are typically conducted in highly controlled research environments, effectiveness studies are conducted in 'real world' treatment settings. The advantage of using this approach is that the results are more representative of 'actual' clinical practice and provide evidence regarding the feasibility of using the intervention as part of ongoing routine care. The research design also includes additional attempts to increase the generalizability of the results by using very inclusive eligibility criteria.

Previous trials of the SHADE program have used therapists to support the delivery of the program [25,26]. This has included the delivery of a one-session intervention at the commencement of treatment and 10-minute 'check in' sessions at the conclusion of each computer session. Possible advantage of such an approach are that therapists can check participants understanding of the intervention, confirm homework assignment, and therapists can address any motivational issues. It has been suggested that therapist support is likely to improve client utilisation of computer interventions and subsequently improve client outcomes [18]. However, a decision has been made in this study to not provide therapist support in the delivery of the program. This is in line with previous computer delivered interventions for substance abuse clients [44] and likely reflects more closely how interventions would ultimately be implemented within routine care.

A further strength is that the research design includes an active attention control condition. A computer delivered typing tutor will be used as the control, with participants being provided with the rationale that improving their typing skills will help their future employment opportunities. This active control has previously been used in computer based trials in residential alcohol and other substance abuse treatment settings [31], and addresses limitations with previous clinical trials in which comparisons have only been made to no-treatment conditions [22].

A significant challenge for this project will be participant dropout due to participants leaving the residential treatment facility prior to completing the intervention. Dropout rates from substance abuse treatments are extremely high. Fifty-seven percent of participants prematurely leave within the first 3-months of treatment [50]. Similar percentages have also been reported in the broader alcohol and other substance abuse treatment literature [see [51] for review]. To help address this concern, participants will complete the SHADE or computer delivered typing interventions twice a week (i.e. over a 5-week period). This represents a shift from the protocol used by Kay-Lambkin et al. [25], where SHADE was delivered weekly for 10-weeks.

A further challenge for the study will be retaining participants at follow-up. People with alcohol and other substance abuse disorders are traditionally very difficult to follow-up. This is further complicated with residential facilities, as participants often move outside of their local area to attend treatment. Attempts to improve follow-up rates in the current study will include using telephone follow-up, obtaining contact details of significant others to help with locating participants, reinforcing to participants the importance of conducting follow-up and financially compensating participants for the time required to complete the assessments (AUD$20).

